^. PK modelling of the oral administration of 4 g of TXA resulted in a plasma concentration of 10 mg/L within 15 min (data on file). If absorption was similarly rapid in pregnant women, this would strongly suggest the IM and oral routes as potential alternatives to IV use.

Recently, the Trauma-INTACT trial (ClinicalTrials.gov:
NCT03875937) assessed the PK of TXA administered intramuscularly in bleeding trauma patients
^
14
^. The study found that the time to reach therapeutic concentrations of 10 mg/L after intramuscular injection of 1 g TXA was within 15 min. Additionally, it was well tolerated with only mild injection site reactions and no serious adverse events reported. The PharmacoTXA trial (ClinicalTrials.gov:
NCT03777488) has assessed the PK of TXA administered intramuscularly or orally in healthy volunteers. An ongoing RCT called TRACES (TRAnexamic Acid to Reduce Blood Loss in Hemorrhagic CESarean Delivery) aims to assess the PK and pharmacodynamics (PD) effects of two doses of TXA (0.5 and 1 g) injected intravenously in women with an ongoing PPH after delivery
^
15
^.

Physiologic changes induced by pregnancy and childbirth
^
16
^ may alter the PK and PD properties of medicines, in particular due to the increase in renal elimination clearance and volume of distribution.

PPH can occur without warning in most women. However, some risk factors such as multiple pregnancy, macrosomia or previous PPH, are known to be associated with an increased risk of PPH
^
17,
18
^.

In this study we will assess the PK, PD, safety and efficacy of TXA administered by IV, IM or oral routes in women giving birth by caesarean section (CS) with at least one risk factor for PPH. Blood samples will be taken from the women immediately before the administration of TXA (1 hour before CS) and at different time points during 24 hours after receipt of intervention. Blood samples from the umbilical cord after clamping and from newborns (obtained from the sample taken for routine heel prick test) will be taken to measure the amount of TXA transferred from the mother to the neonate via the placenta. The efficacy of the different routes of TXA administration in preventing blood loss, reducing fibrinolytic activity, and the safety of the interventions will be evaluated.

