### Description of investigational product and justification of the dosage, route of administration, administration schedule and treatment duration

In this study, women will be randomised to four groups:

1.
**IV TXA GROUP:** 30 women will receive 1 g of TXA by IV route. IV TXA treatment rapidly achieves the plasma levels of TXA needed to inhibit fibrinolysis and prevent excessive bleeding. Pharmacological research has shown that an IV dose of 1 g TXA maintains therapeutic plasma levels for around 3 hours, the period when the risk of bleeding is greatest
^
12,
19
^. However, the TXA PK and PD in pregnant women has not been described so far.2.
**IM TXA GROUP:** 30 women will receive 1 g of TXA by IM route. Studies of IM TXA in healthy volunteers report good absorption and no adverse effects
^
11,
12
^. The dose will be given as two 5 mL (0.5 g each) injections into the thigh (rectus femoris or vastus lateralis) or buttocks (gluteal muscles) muscles, depending on a clinical assessment of muscle mass
^
12
^. The 1 g dose (10 mL) is divided to reduce the volume injected (5 mL is considered the upper limit)
^
20
^. The injections will be given using the most appropriate needle size for IM administration from the sites stock (1" between 19 - 25 gauge and from 1 ½ inches up to 3" for large adults) using the Z-track method to seal the medication in the muscle
^
20
^.3.
**TXA SOLUTION ORALLY:** 30 women will receive 4 g of TXA oral solution. The dose was selected because of the 50% oral bioavailability and because previous and preliminary PK data show that the absorption through the oral route is much slower than through the IV or IM routes, with much lower maximal concentration (Cmax)
^
12,
13,
19,
21
^. Therefore, higher doses are needed to reach therapeutic levels, according to simulations. The oral route (tablets or solutions) is well characterised
^
22–
24
^, but oral TXA PK and PD in pregnant women have not been described so far.4.
**NO TXA CONTROL:** 30 women will receive no TXA and will be the control group for PD, blood loss and safety data.

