^. This review confirmed that there are no reports of adverse neonatal outcomes associated with the administration of TXA shortly before giving birth to prevent PPH
^
42
^. A systematic review on the effectiveness and safety of the use of TXA to prevent PPH that included 25 studies with a total of 4,747 participants concluded that there was no increased risk of deep vein thrombosis and an increased risk of minor transient events, i.e. nausea, vomiting, headache or dizziness
^
44
^. The included studies that evaluated the safety of TXA on neonates reported that no adverse events occurred, and the Apgar score that assesses the baby’s health immediately after birth showed no difference between babies in TXA-treated and control groups
^
44
^.

No mutagenic activity of TXA has been detected
*in vitro* and
*in vivo* test systems
^
45
^. No foetal abnormalities were identified in early dysmorphology and reproductive studies in animals
^
45–
47
^.

As the TXA will be delivered at the end of the 3rd trimester of pregnancy when the foetal development is complete, the trial treatment will not have any impact on foetal development.

The foreseeable risks related to the IM route of administration may include pain, redness and bruising at the injection site and a rare risk of infection at the injection site.

The study also involves additional blood samples from all participants. We will take the smallest possible volume of blood that will allow us to carry out the analysis. The total volume of blood taken from the participating women (maximum of 35 mL over 24 hours) should have no clinical impact on the participant. One blood sample (2 × 10 µl) will be taken from the neonate at the time of the routine heel prick test.

We will routinely assess all women for nausea, vomiting, diarrhoea, thrombotic events, seizures and injection site reactions as secondary outcomes. Additionally, all neonates will be routinely assessed for birth complications and adverse events.

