### Premature exit of trial participant

Participants may exit the study at any time and for any reason. A previously given consent can be withdrawn. The investigator can withdraw a participant from the trial for any safety reason or if it is in the participant's best interest.

If a participant exits the trial prematurely or withdraws consent or refuses consent for continuation, data collected up to time of premature exit will be used. Participants who withdraw from the trial with less than six post treatment PK samples will be replaced to ensure the four intervention groups remain balanced.

**
*Monitoring participants after the premature termination of treatment.*
** In case of an adverse event to the participant or her baby, the investigator will complete an adverse event report and monitor the event until the end of her participation in the research or until it has resolved or reached a stable state.

**
*Procedure for replacing participants.*
** If consent procedures are complete but the TXA dose is not given in full, the participant will be replaced.

When oral TXA is given and the participant vomits within the first hour of receiving the intervention, this participant will be replaced in the study. However, data collection for the participant will continue to the trial end.

Where the CS is delayed and takes place more than 2 hours after the administration of the intervention, the participant will be replaced in the study. However, data collection for the participant will continue to the trial end.

If a participant receives the TXA dose but there are less than six post treatment evaluable PK samples obtained after TXA administration, this participant will be replaced in the study. However, data collection for the participant will continue to the trial end.

Data collected from the replaced participants will be used.

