### Planned recruitment rate

Pregnant women will be enrolled until 120 participants with fully evaluable data are included. Evaluable participants must receive the full dose, not vomit the oral dose within 1 hour of administration, and have at least six post randomisation PK blood samples.

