### Pharmacokinetic analysis

All participants who receive the full dose of TXA and did not vomit the oral dose within the first hour and have at least six PK samples obtained after TXA administration to determine maternal plasma concentrations of TXA will be included in the PK data analysis. The actual blood sampling times will be recorded and used in calculations for PK parameter estimation. 

TXA time-courses will be analysed using the nonlinear mixed effect modelling software program
Monolix 2020R1 version
^
53
^, as previously described
^
52,
54–
56
^. Briefly, parameters will be estimated by computing the maximum likelihood estimator of the parameters without any approximation of the model (no linearization) using the stochastic approximation expectation maximization (SAEM) algorithm combined to a Markov chain Monte Carlo (MCMC) procedure (to ensure full convergence, the MCMC will be fixed to 20 and the iteration number to 1000). Different error models will be investigated (i.e. multiplicative, proportional and/or additive error models) to describe residual variabilities (expressed as σ, square root of σ
^2^), and the between-subject variabilities (expressed as ω, square root of the variance ω
^2^) will be ascribed to an exponential model. The Bayesian information criterion (BIC) will be used to test different hypotheses regarding the model, i.e.:

i.covariate effect(s) on pharmacokinetic parameter(s)ii.residual variability model (proportional versus proportional plus additive model)iii.structure of the variance-covariance matrix for the ω parameters.

Main covariates of interest in the population will be age, bodyweight (BW) and renal function, IV fluid and blood transfusion volume. Parameter estimates will be standardised for a mean standard covariate using an allometric model: P
_i_ = P
_STD_ x (COV
_i_/COV
_STD_)
^PWR^ where P
_STD_ is the standard value of parameter and P
_i_ and COV
_i_ are the parameter and covariate values of the i
^th^ individual. The PWR exponents may be estimated from the data. However, for bodyweight, allometric scaling theory dictates that these are typically 0.75 and 1 for clearance and volumes terms, respectively
^
46
^. The goodness-of-fit of each model will be evaluated by visual inspection of the individual concentration-time courses, the observed-predicted (population and individual) concentration scatter plots and the prediction-corrected visual predictive checks.

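### Vomiting of the oral dose counts as dose loss only within 1 hour; no absorption figure supports that limit, and later losses would be modelled as a full 4 g dose

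*Protocol article*

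**What the plan says.** The 1-hour limit appears in three places and is the same in each.

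- Procedure for replacing participants (under Premature exit of trial participant): "When oral TXA is given and the participant vomits within the first hour of receiving the intervention, this participant will be replaced in the study".
- Planned recruitment rate: an evaluable woman must "not vomit the oral dose within 1 hour of administration".
- Pharmacokinetic analysis: the set is "All participants who receive the full dose of TXA and did not vomit the oral dose within the first hour" and who have at least six post-dose PK samples.

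Elsewhere, the justification of the oral dose says that "absorption through the oral route is much slower than through the IV or IM routes" and uses 50% oral bioavailability. The Background reports modelling in which 4 g by mouth "resulted in a plasma concentration of 10 mg/L within 15 min", and the Hypothesis section puts the time to 10 mg/L at about 30 minutes. TXA is given about 1 hour before surgery, and a woman is replaced if surgery starts more than 2 hours after dosing. The safety section lists vomiting among the commonest side-effects and states "We will routinely assess all women for nausea, vomiting, diarrhoea, thrombotic events". The main PK covariates named are age, bodyweight, renal function, IV fluid and transfusion volume.

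**The concern.** The protocol already accepts that vomiting can invalidate an oral dose, because it removes early vomiters from the PK set. It stops counting at 60 minutes without showing how much drug is still unabsorbed then. Surgery, by design, begins at about that moment or in the hour after it, so vomiting around the operation will often fall just outside the window.

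A woman who vomits at, say, 90 minutes meets every stated condition. The model is told that she had 4 g, so lost drug can only appear as lower bioavailability, altered absorption or between-woman variability. Drug given IV or IM cannot be lost this way, so the error would fall on one arm of the route comparison. The primary objective is the population PK of the three routes, which makes oral bioavailability and exposure central results.

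**Working it through.** **The plan's own figures.** The arms check: 4 × 30 = 120. The precision claim (relative standard errors below 30%) cannot be reproduced, because the parameters and variances given to the design software are not in the article. The vomiting rule has no figure attached.

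**Inputs from the protocol.** Oral dose 4 g; bioavailability F = 0.50, so 2,000 mg absorbable; half-life 1–2 h; 10 mg/L within 15 min (Background) or about 30 min (Hypothesis); post-dose samples at 15 min, 30 min, 1, 2, 4, 8, 12 and 24 h; 30 women in the oral arm.

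**Assumptions, not in the protocol.** One compartment with first-order absorption; distribution volume V of 10–50 L; proportion p of oral women vomiting after 1 h; share e of unabsorbed drug expelled, 25–100%.

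**Step 1: how much could remain at 1 hour?** Solve for ka in

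C(t) = 2000·ka / [V(ka − ke)] × (exp(−ke·t) − exp(−ka·t)) = 10 mg/L, with ke = ln 2 / half-life.

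The unabsorbed share is then U = exp(−ka × time). Ranges within a cell cover half-lives of 1–2 h.

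| 10 mg/L reached at | V (L) | ka (per h) | U at 1 h | U at 1.5 h | U at 2 h |
|---|---|---|---|---|---|
| 15 min | 10 | 0.21–0.22 | 80–81% | 71–72% | 64–65% |
| 15 min | 30 | 0.68–0.72 | 49–51% | 34–36% | 24–26% |
| 15 min | 50 | 1.21–1.28 | 28–30% | 15–16% | 8–9% |
| 30 min | 10 | 0.11–0.12 | 88–89% | 83–85% | 78–80% |
| 30 min | 50 | 0.64–0.71 | 49–53% | 34–38% | 24–28% |

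These are upper bounds on U. The protocol says 10 mg/L is reached within the stated time, so ka may be larger. At ka = 2–3 per h only 14–5% remains at 1 h and 5–1% at 1.5 h. Drug that has already left the stomach cannot be vomited either, which is why e is allowed below 100%.

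**Step 2: effect on mean oral bioavailability.** Measured against the IV arm, one late vomiter has apparent F = 0.50 × (1 − U·e). The arm mean is 0.50 × (1 − p·U·e), a relative bias of −p·U·e.

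| p | U = 0.1, e = 0.25 | U = 0.5, e = 0.5 | U = 0.8, e = 1 |
|---|---|---|---|
| 1 woman in 30 | −0.1% | −0.8% | −2.7% |
| 10% | −0.25% | −2.5% | −8% |
| 20% | −0.5% | −5% | −16% |
| 30% | −0.75% | −7.5% | −24% |

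At p = 10%, mean F lies between 0.499 and 0.460. With the planned exponential between-subject model, the typical value is nearer 0.50 × (1 − U·e)^p. In the worst 10% cell that is 0.50 × 0.2^0.1 = 0.426, so a few women who lose drug pull the typical value further than the mean.

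**Step 3: what is not affected.** The 15 min, 30 min and 1 h samples precede any vomiting after 1 h. The remaining five of the eight post-dose samples may follow it. The six-sample rule does not screen these women out.

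**The case against.** The strongest reply is that nothing here is contradictory. The three sections agree, receiving the full dose and not vomiting early are listed as separate conditions, and the covariates named are only the main ones. A vomiting term or sensitivity run could sit in an analysis plan that is not shown. That stands as far as it goes: the absence of a vomiting covariate from the article is not in itself a fault. What the article does fix is the 1-hour limit in the PK set, with no absorption figure behind it.

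A second reply is that much slower is only relative to IV and IM, and that 10 mg/L within 15 minutes suggests early uptake. This also stands, and it is why the unabsorbed shares above are ceilings.

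A third is that keeping late vomiters describes exposure as it would occur in practice. This is weaker. The protocol removes early vomiters from the PK set, so its target is already the undisturbed dose, and a late vomiter does not match that target.

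A reader might go further and infer that women will lose much of the dose and that oral bioavailability is biased low. The documents give no absorption rate and no vomiting rate, so neither can be asserted. Nor does it follow that vomiting in theatre is never counted: surgery is only about 1 hour after dosing, so some of it may fall inside the window.

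**Conclusion.** The point holds in conditional form. The 1-hour limit is not justified against the protocol's own description of oral absorption, and it closes at about the time surgery starts. Any unabsorbed drug vomited later would be modelled as if absorbed from a full 4 g dose. The direction of the resulting error in oral bioavailability, AUC and later concentrations is downward, with inflated variability, in the oral arm only.

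The size cannot be known from the documents. At a 10% late-vomiting rate the shift in mean bioavailability runs from about 0 to −8%; one woman in 30 moves it by at most about 3%; it is zero if nobody vomits unabsorbed drug after 1 hour. All of these rest on the assumed absorption model, volume, vomiting rate and expelled share. The prediction of 10 mg/L within about 30 minutes is largely untouched. This is worth correcting because the remedy is nearly free, not because serious bias has been shown.

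**What to change.** This changes the analysis only; no dose or clinical rule needs to change.

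1. Record the clock time of any vomiting in the oral arm throughout the absorption period. Vomiting is already assessed in all women, and its timing is already needed to apply the 1-hour rule.
2. Keep women who vomit after 1 hour in the main PK set.
3. Test vomiting after 1 hour as a covariate on oral bioavailability, using the BIC comparison already planned for covariate effects.
4. Whatever BIC selects, report oral F, ka and Cmax in a sensitivity analysis without women who vomited between 1 hour and a later time fixed in advance. Deriving that time from the fitted model would be circular, because the model would have been fitted to the women it then removes.

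An explicit term for drug lost from the absorption depot is not recommended as the main approach: with perhaps a few events among 30 women it may not be estimable.

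The cost is one extra parameter or one extra model run in a 30-woman arm. If nobody vomits late, nothing is lost.

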## Rationale

### Hypothesis

We hypothesise that IM and oral solution of TXA will be well absorbed in pregnant women. Based on PK modelling of data available in the literature, we predict that a 1 g IM injection or 4 g oral solution administration of TXA will provide therapeutic TXA levels ≥10 mg/L in plasma
^
10
^ within about 30 minutes. 

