### Primary endpoint

Blood TXA concentrations over time in pregnant women.

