**Figure 3. f3:**
[figure not shown]
Timing of biological samples.

*Pharmacokinetics*: Finger prick blood samples (2 × 10 µL per sample) for TXA quantitation will be taken as per
Figure 3.

*Pharmacodynamics*: Blood samples (3 mL of venous blood in tubes containing 3.2% sodium citrate) for D-dimer quantitation will be taken as per
Figure 3.

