### Collection and storage of biological samples

Only one blood sample for PK analysis will be collected at baseline for women who are randomised to receiving no TXA. Samples for D-dimer, full blood count (FBC) and renal function will be collected.

Maternal blood will be taken from a cannula to avoid multiple venepuncture as follows:

Two samples of 3mL each will be taken for FBC and two samples of 3mL each for renal function. Blood samples will be collected in purple top EDTA tubes for FBC and yellow top tubes with separation gel and clot activator for renal function.

Five samples for D-dimer of 3 mL for each sample of blood to be taken in collection blue top tubes containing 3.2% sodium citrate. Blood samples for D-dimer, FBC, and renal function will be collected from the hospitals and analysed by a local central laboratory. The laboratory will be asked to store the sample used for D-dimer analysis until the end of trial to allow for repeat tests if needed. In the event of failure of any of the PK samples, this will be used as a back-up and will be destroyed at the end of the trial.

Each maternal PK sample require about 20 µL of blood taken using a Mitra
^®^ cartridge from a finger prick (2 × 10 µL samples taken on the 2 cartridges of the same device to have one primary and one confirmation sample if needed). Sites will be provided with written procedures on how to obtain the blood sample using the Mitra
^®^ cartridge. Cartridges will be labelled with the date and time the sample was taken and with the participant Study Identification number.

The total volume of blood taken (less than 35 mL) should have no clinical impact on the participant.

To obtain the umbilical PK blood sample, once the umbilical cord is clamped, it is wiped with antiseptic and a syringe and needle is inserted into the vein in the umbilical cord to withdraw a small amount of blood. PK samples from the umbilical cord and neonates will also be taken using the Mitra
^®^ cartridge system as described above.

A blood sample from the neonate (2×10 µL) will be taken using the Mitra
^®^ cartridge at the time of the routine clinical heel prick test to avoid additional heel pricks.

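### The primary PK quantity is named as blood in the sampling and endpoint sections but as plasma in the analysis and the 10 mg/L benchmark, with no stated link between the two

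*Protocol article*

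**What the plan says.** All references are to the protocol article.

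- **Sampling.** The text under Figure 3 specifies "Finger prick blood samples (2 × 10 µL per sample) for TXA quantitation will be taken as per" the figure. Collection and storage of biological samples adds: "Each maternal PK sample require about 20 µL of blood taken using a Mitra" cartridge. No step separating plasma is described.
- **Endpoint.** Primary endpoint reads "Blood TXA concentrations over time in pregnant women".
- **Analysis.** Pharmacokinetic analysis defines who enters the PK dataset by a minimum number of "PK samples obtained after TXA administration to determine maternal plasma concentrations of TXA".
- **Benchmark.** Hypothesis predicts that the IM and oral doses "will provide therapeutic TXA levels ≥10 mg/L in plasma" within about 30 minutes. Background also gives the therapeutic level as a plasma value.
- **Back-up.** The D-dimer sample is venous blood in a 3.2% citrate tube and is stored. Collection and storage says of it: "In the event of failure of any of the PK samples, this will be used as a back-up".
- **Covariates.** Pharmacokinetic analysis lists age, bodyweight, renal function, IV fluid volume and transfusion volume as the main ones. Haematocrit is not among them, although two full blood counts per woman are planned.
- **Assay.** Blood sample analysis gives the range, accuracy and precision but names no matrix.

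**The concern.** One quantity, the primary one, carries two names that are interchangeable only if TXA is equally concentrated in red cells and plasma. The endpoint and the sampling sections say blood; the analysis section says the same samples give plasma concentrations. Followed as written, blood readings would be reported as plasma and set beside a plasma benchmark.

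The Abstract gives the main aim as finding out whether IM and oral TXA reach levels that inhibit fibrinolysis, and 10 mg/L in plasma is the only such level the article supplies. That absolute comparison is the result most exposed to a matrix error. Absolute clearance and volume are exposed too, as is their comparison with the published parameters used in the Sample size calculation.

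The back-up provision adds a second, smaller problem. A citrated venous sample differs from finger-prick blood in site and in dilution, and possibly in matrix. If it stood in for a failed sample without adjustment, one woman's curve would mix two scales.

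**Working it through.** There is no plan figure to reproduce: 10 mg/L is a cited level, not a calculated one.

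**Inputs from the article.** Plasma benchmark 10 mg/L (Hypothesis); serum half-life 1–2 h (Safety of TXA); finger-prick blood as the PK sample; 3.2% citrate in the back-up tube.

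**Assumed inputs, not in the article.** Haematocrit H from 0.30 to 0.40; red-cell:plasma concentration ratio K from 0 to 1, with 1.2 added to show the sign change; citrate at 1 part to 9 parts blood.

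**Step 1: blood relative to plasma.** By mass balance, R = 1 − H + H × K. For example, at H = 0.40 and K = 0, R = 1 − 0.40 = 0.60. Clearance and volume scale as dose over concentration, so treating blood as plasma multiplies both by 1/R. Each cell below gives H = 0.30, then H = 0.40.

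| K | R | Plasma 10 mg/L reads as | Blood reading of 10 mg/L means, in plasma | Factor on clearance and volume |
|---|---|---|---|---|
| 0 | 0.70, 0.60 | 7.0, 6.0 | 14.3, 16.7 | 1.43, 1.67 |
| 0.5 | 0.85, 0.80 | 8.5, 8.0 | 11.8, 12.5 | 1.18, 1.25 |
| 1 | 1.00, 1.00 | 10.0, 10.0 | 10.0, 10.0 | 1.00, 1.00 |
| 1.2 | 1.06, 1.08 | 10.6, 10.8 | 9.4, 9.3 | 0.94, 0.93 |

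**Step 2: time above 10 mg/L.** With mono-exponential decline, the apparent time lost is half-life × log2(1/R). At K = 0:
- R = 0.70: 30.9 min (half-life 1 h) or 61.7 min (2 h).
- R = 0.60: 44.2 min (1 h) or 88.4 min (2 h).

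At K = 1 the loss is zero.

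**Step 3: comparisons between routes.** Relative bioavailability is a ratio of dose-adjusted exposures, so a constant R cancels. A constant scale factor also leaves the absorption rate unchanged. Only variation in R over time or between women would remain.

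**Step 4: the citrated back-up.** The article does not say whether it would be assayed as blood or as plasma.
- As citrated whole blood, it reads 0.90 of undiluted blood.
- As citrated plasma at K = 0, it reads 0.9(1 − H) / [0.9(1 − H) + 0.1] of true plasma: 0.63/0.73 = 0.863 at H = 0.30 and 0.54/0.64 = 0.844 at H = 0.40. Relative to finger-prick blood that is 0.863/0.70 = 1.23 and 0.844/0.60 = 1.41.
- As citrated plasma at K = 1, it reads about 0.84 to 0.86 of blood if red cells and diluted plasma do not re-equilibrate, and 0.90 if they do.

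A substituted value could therefore sit anywhere from about 16% below to about 41% above the finger-prick scale.

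**The case against.** The strongest reply is that the size and direction of any bias are unknown. The ratio is not in the article, the assumed range includes no bias at all, and a ratio above 1 reverses it. This stands. A reader might infer that the trial's answer is biased against the IM and oral routes; the article supports that only conditionally.

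Second, 10 mg/L appears in the Background and Hypothesis, while the analysis sections define no test, proportion or time-to-threshold against it, and the word plasma occurs in a clause about who is analysed. This also stands, so it would be wrong to say that the plan formally judges the routes against that level. But the Abstract's aim and the Discussion's appeal to therapeutic levels make an informal reading against it almost certain.

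Third, a reader might infer that no conversion exists and that back-up samples are pooled with the rest. Neither is stated. The modelling follows cited sources, and the complete protocol is in an additional file; both are outside the documents reviewed. A condensed article may leave such details there. It remains that the article's own sections contradict each other on what the primary quantity is.

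Fourth, the harm is limited. A constant ratio largely cancels between routes, fluid and transfusion volumes are already covariates, each PK device holds a second cartridge that may make back-ups rare, and over most of the assumed range the error is conservative for the IM and oral routes. All fair. These points narrow the consequence to absolute parameters and the reading against 10 mg/L.

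**Conclusion.** The contradiction is established from the article alone: blood in the sampling and endpoint sections, plasma in the analysis section and in the benchmark. Its effect is conditional. If TXA concentrations in blood and plasma are equal, or a conversion is applied, there is none. Otherwise absolute clearance, absolute volume and any reading against 10 mg/L are biased.

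For H of 0.30–0.40 and K of 0–1, a plasma level of 10 mg/L reads as 6.0–10.0 mg/L in blood, and clearance and volume are inflated by a factor of 1.00–1.67. Attainment of 10 mg/L would be understated and the time to reach it lengthened. Above K = 1 these effects reverse. Comparisons between routes are largely safe under a constant ratio. Handling of the citrated back-up is unstated, not shown to be wrong. The point should be settled before the PK analysis because it concerns the primary endpoint and is cheap to resolve.

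**What to change.** 1. Name blood as the matrix in both Primary endpoint and Pharmacokinetic analysis.
2. Link the result to the benchmark in one of two ways. Either convert to plasma-equivalent concentrations with a stated blood-to-plasma ratio and the haematocrit from the full blood counts already taken, or restate the 10 mg/L level for blood. If no validated ratio is available, report the result over a range of plausible ratios.
3. Flag every citrated venous back-up value. Correct it for matrix and citrate dilution, or give it its own scale factor in the model, and report a sensitivity analysis without these values.

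The cost is some wording, a little extra analysis and one added assumption about the ratio. With only two blood counts per woman, the haematocrit adjustment cannot follow changes across all 24 hours, and the report should say so.

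Estimating the ratio within the trial from stored D-dimer samples paired with finger pricks is optional. Those samples are kept at a local central laboratory for repeat tests and back-up and are then destroyed, while TXA is assayed at a separate university laboratory. Bridging would therefore need a new permitted use and shipment.
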